# Modified quadruple therapy versus bismuth-containing quadruple therapy in first-line treatment of *Helicobacter pylori* infection in Korea; rationale and design of an open-label, multicenter, randomized controlled trial

**DOI:** 10.1097/MD.0000000000013245

**Published:** 2018-11-16

**Keywords:** bacterial, bismuth, disease eradication, drug resistance, *Helicobacter pylori*

## Abstract

**Background::**

Clarithromycin-containing triple regimen for eradication of *Helicobacter pylori* is no longer acceptable in Korea due to high clarithromycin resistance. Concomitant therapy or bismuth-containing quadruple therapy is recommended as an alternative regimen. A recent study in Korea has shown that modified quadruple therapy has comparable efficacy and safety to concomitant therapy as a first-line regimen. However, there has been no comparative study of modified quadruple therapy with bismuth-containing quadruple therapy. The aim of this study is to compare the efficacy and safety of modified quadruple therapy with those of bismuth-containing quadruple therapy as a first-line regimen and to present the phenotypic and genotypic antibiotic resistance profile of *H pylori*.

**Methods::**

This study is an open-label, multicenter, randomized controlled trial. We are recruiting subjects endoscopically diagnosed with *H pylori* infection from 2 hospitals in Korea. Subjects will be randomly allocated either to modified quadruple therapy (proton-pump inhibitor bid, amoxicillin 1 g bid, metronidazole 500 mg tid, bismuth subcitrate 300 mg qid daily) or bismuth-containing quadruple therapy (proton-pump inhibitor bid, tetracycline 500 mg qid, metronidazole 500 mg tid, bismuth subcitrate 300 mg qid daily) for 14 days. The rate of eradication success and adverse events will be checked at least 4 weeks after the treatment. Antibiotic resistance will be established using both a bacterial culture with agar dilutions and DNA sequencing of the clarithromycin resistance point mutations in the 23S rRNA gene of *H pylori.*

**Conclusion::**

The results of this study will provide solid evidence for determining the optimal treatment regimen for first-line *H pylori* eradication in Korea.

## Introduction

1

*Helicobacter pylori* is the most important pathogen in the development of gastric cancer.^[1,2]^ Infection with *H pylori* causes chronic atrophic gastritis, intestinal metaplasia, low- and high-grade dysplasia, and gastric cancer in sequence.^[3]^ Previous studies have shown the primary and secondary preventative effects of *H pylori* eradication in the development of gastric cancer,^[4–7]^ and eliminating this pathogen is considered the most promising strategy for the prevention of this disease.^[8]^

South Korea has the highest incidence of gastric cancer worldwide, and *H pylori* infection is still prevalent.^[9–11]^ Clarithromycin-containing triple therapy is the primary regimen approved and reimbursed by the Korean National Health Insurance Service.^[12]^ However, due to high clarithromycin resistance in Korea, the current eradication rate of clarithromycin-containing triple therapy has fallen below 80%, which is not acceptable as a first-line eradication regimen.^[9,13–15]^ Concomitant therapy or bismuth-containing quadruple therapy is recommended as an alternative regimen.^[8,9,12]^ However, concomitant therapy is not recommended in regions with high metronidazole resistance, and the resistance rate of metronidazole has been reported to be as high as 66% in Korea.^[9,16]^ Moreover, dual clarithromycin and metronidazole resistance undermines the efficacy of concomitant therapy, and there is no definite 2nd-line or 3rd-line rescue regimen for patients who do not respond to the above therapies.^[17,18]^ Therefore, finding an optimal regimen for 1st-line eradication is warranted in Korea.

A recent study in Korea has shown that modified quadruple therapy (proton-pump inhibitor (PPI), amoxicillin, metronidazole, bismuth subcitrate) has rates of eradication success and adverse events comparable to those of concomitant therapy.^[19]^ However, this study did not explore the antibiotic resistance profile of *H pylori*, and there has been no comparative study of modified quadruple therapy with bismuth-containing quadruple therapy. The aim of this study is to compare the efficacy and safety of modified quadruple therapy and bismuth-containing quadruple therapy and to present the phenotypic and genotypic antibiotic resistance profile of *H pylori*.

## Methods

2

### Overview of the trial design

2.1

Within this open-label, multicenter, randomized controlled, parallel-group trial, subjects with *H pylori* infection will be randomly assigned either to modified quadruple therapy (PPI bid, amoxicillin 1 g bid, metronidazole 500 mg tid, bismuth subcitrate 300 mg qid daily) or bismuth-containing quadruple therapy (PPI bid, tetracycline 500 mg qid, metronidazole 500 mg tid, bismuth subcitrate 300 mg qid daily) for 14 days. The eradication success rate, adverse events related to the medications and compliance will be investigated and compared between the 2 therapies. Phenotypic and genotypic antibiotic resistance testing will be performed during the trial, and these data will be used in the interpretation of the results.

Participants will be recruited from 2 Hallym University-affiliated Hospitals (Hallym University Chuncheon Sacred Heart Hospital in Chuncheon city, Hallym University Sacred Heart Hospital in Anyang city), and the recruitment period is from August 2018 to July 2019. Data will be collected from the subjects following their 1st hospital visit post-regimen (2 weeks after enrollment, after ending their eradication regimen) to check for adverse events related to the medications and for drug compliance and following their 2nd visit post-regimen (6 weeks after enrollment) to determine eradication success and to check for potential adverse events. The visit window is 1 week.

### Study subjects

2.2

Subjects who undergo upper gastrointestinal endoscopy within 3 months and are proven to have *H pylori* infection either by the rapid urease test, the ^13^C-urea breath test (UBT), or a histological examination will be included in this trial. Exclusion criteria are as follows:

1.participants who have a history of *H pylori* eradication;2.participants who have undergone a stomach resection;3.participants who have a history of allergy or adverse events related to the eradication medications;4.participants who have taken a PPI within 2 weeks or a histamine 2 receptor antagonist (H2RA) within 1 week;5.participants who have taken aspirin (except low-dose aspirin for primary prophylaxis of cardiovascular disease), intravenous or oral nonsteroidal anti-inflammatory drugs, anticholinergics, prostaglandin analogs, pro-motility drugs, or sucralfate within a week or participants who need a continuous administration of those drugs;6.participants who have taken antibiotics within 4 weeks;7.pregnant or breast-feeding participants or participants who do not wish to avoid pregnancy during the clinical trial;8.participants who are currently taking lovastatin, simvastatin, atorvastatin, indinavir, ritonavir, cyclosporin, terfenadine, pimozide, astemizole, human immunodeficiency virus protease inhibitors (atazanavir, nelfinavir), ergotamine, dihydroergotamine, mizolastine, bepridil, or ticagrelor;9.participants who have infectious mononucleosis, a central nervous system infection, a hematological disease, galactose intolerance, Lapp lactase deficiency, glucose-galactose malabsorption, or Torsades de pointes; and10.participants who are less than 18 years of age.

### Outcome measurement

2.3

The *H pylori* infection is diagnosed by 1 or more of the following methods: the rapid urease test, the UBT or a histological examination. Two specimens from the gastric corpus and antrum will be taken during an endoscopy for the rapid urease test (Pronto Dry New; Medical Instruments Corp., Herford, Germany) or a histological assessment using Giemsa staining. A UBT (UBiT-IR 300; Otsuka Pharmaceutical Co., Ltd, Tokyo, Japan) measuring exhalation of ^13^CO_2_ before and 30 minutes after ingestion of 75 mg of ^13^C-marked urea will be performed. An initial breath sample will be obtained after at least an 8-hour fasting period (overnight fasting). The UBT after eradication of *H pylori* will be performed at least 4 weeks after the eradication therapy has ended. Delta over baseline >2.5% will be considered positive. Subjects who take medications that may affect the outcome of the UBT (e.g., PPI, H2RA, antibiotics) after the end of the eradication regimen will be tested at least 4 weeks after stopping these medications (the wash-out period is at least 4 weeks). In this case, the routine follow-up period for the 2nd visit (6 weeks after enrollment) will be prolonged assuming no violation of the study protocol has taken place.

All the subjects will be educated about common adverse events related to the eradication medications, and they will be asked to submit self-report questionnaires about adverse events related to the eradication medications at the 1st visit (2 weeks after enrollment, after ending the eradication regimen) and at the 2nd visit (6 weeks after enrollment, for UBT checking). The severity of the adverse events is defined as “mild” (transient and well tolerated), “moderate” (causing discomfort and partially interfering with daily activities), or “severe” (causing considerable interference with daily activities) and will be taught to the subjects for reporting as described above.^[20]^ Potential adverse events will be monitored by the research staff for 3 months after enrollment. Information about adverse events related to the eradication medications will also be gathered through interviews conducted by the doctors and independent staff at the 1st and 2nd visits. Compliance with the eradication regimen will be checked at the 1st visit by independent staff.

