### Statistical analysis

2.6

The sample size was calculated by using an α-error <0.05 and a β-error <0.2 for a 2-tailed significance test. The calculated number of subjects required for the trial is 100 in each arm, which was determined by assuming an eradication rate of 96.2% from treatment with bismuth-containing quadruple therapy for 14 days as seen in a previous study in Korea (per-protocol (PP) analysis), an equivalence margin of 8%, and a dropout rate of 10%.^[24]^

For the intention-to-treat (ITT) analysis, all participants who take at least the 1st dose of prescribed medications will be included and assessed and for the modified ITT analysis, all participants who take at least the 1st dose of prescribed medications and who are in the posttreatment *H pylori* status will be included and assessed. For the PP analysis, only those who maintain and complete treatment with the prescribed medications without violating the regulations (violation is <80% medication compliance; poor adherence to medication is defined as taking less than 80% of what is prescribed) will be included and assessed (Fig. 1).

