A recent study in Korea has shown that modified quadruple therapy has rates of eradication success and adverse events comparable to those of concomitant therapy.^[19]^ Characterizing the regional antibiotic resistance profile is important for *H pylori* eradication because antibiotic resistance is the chief cause of treatment failure. However, the study above did not explore antibiotic resistance profiles, making it difficult to interpret its results. A previous study has also shown that modified quadruple therapy is comparable to bismuth-containing quadruple therapy as a rescue regimen for patients with at least 2 consecutive treatment failures.^[20]^ Additionally, modified quadruple therapy has been shown to have high eradication success even in subjects with amoxicillin, metronidazole, or clarithromycin resistance, and this therapy has fewer adverse events and higher compliance than does bismuth-containing quadruple therapy.^[20]^

This study will compare the efficacy and safety of modified quadruple therapy and bismuth-containing quadruple therapy as well as presenting the phenotypic and genotypic antibiotic resistance profile of *H pylori*. The strength of this study resides in providing evidence regarding the efficacy and safety of using modified quadruple therapy as a 1st-line regimen in different regions of Korea compared to previous reports (a previous study was conducted in Seoul as a single center study; however, we will recruit patients in Gangwon and Gyeonggi provinces) and additionally, in providing evidence on the use of bismuth-containing quadruple therapy as a 1st-line treatment, which has been scarce as a 1st-line treatment in Korea. Moreover, with the comparative results of the antibiotic-susceptibility gold standard ‘agar dilution’ method vs. DNA sequencing of the clarithromycin resistance point mutations in the 23S rRNA of *H pylori*, it will be possible to interpret the outcome of this study in light of the antibiotic resistance profiles of *H pylori* including the unknown clinical significance of point mutations, such as G2141A, A2144T, or T2182C.

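### A non-study antibiotic taken before the breath test only delays the test, so a compliant participant it cures stays in the per-protocol set as a success of the allocated arm

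*Protocol article*

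**What the plan says.** Section 2.3 (Outcome measurement) covers "Subjects who take medications that may affect the outcome of the UBT (e.g., PPI, H2RA, antibiotics) after the end of the eradication regimen". These participants "will be tested at least 4 weeks after stopping these medications (the wash-out period is at least 4 weeks"). The second visit, normally 6 weeks after enrollment, "will be prolonged assuming no violation of the study protocol has taken place". Antibiotics, PPI and H2RA share this rule. It sets no limit on the type of antibiotic or the reason for taking it, and it attaches no consequence other than the delay.

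Section 2.6 (Statistical analysis) defines the three analysis sets:

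- ITT: "all participants who take at least the 1st dose of prescribed medications will be included and assessed".
- Modified ITT: the same, restricted to those "who are in the posttreatment *H pylori* status will be included and assessed".
- PP: those who complete treatment without violating the rules, where "violation is <80% medication compliance; poor adherence to medication is defined as taking less than 80% of what is prescribed".

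No set carries a condition on antibiotics taken after the study regimen. The only restriction on antibiotics in the article is an entry criterion in section 2.2, covering the 4 weeks before entry.

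**The concern.** The washout is the right tool for a PPI or H2RA, which can make the breath test falsely negative for a time. An antibiotic can do that too, but it can also clear the infection. In that case the test after the washout is truly negative, and waiting longer does not change it.

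The trial asks whether the allocated regimen eradicates H pylori. The PP set is where that question should be cleanest, and the sample size rests on a PP eradication rate. A cure achieved by a drug outside the trial is not evidence about either regimen, yet the stated rules credit it to the arm, in PP as well. Few failures are expected, so each one reclassified as a success carries some weight.

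**Working it through.** **1. A compliant participant, traced through the text.** Take someone who took at least 80% of the regimen, is still infected, and is then given a systemic antibiotic for another reason before the UBT.

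- Section 2.3: the UBT is delayed at least 4 weeks. The proviso is met, because the only violation defined is "violation is <80% medication compliance".
- If the antibiotic only suppressed the infection, it returns during the wait and the test is positive. That classification is correct.
- If the antibiotic cleared the infection, the test is negative.
- Section 2.6: the participant took a first dose (ITT), has a known status (modified ITT) and was compliant (PP). The negative test counts as eradication by the allocated arm in all three sets.

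The proviso cannot be read as making antibiotic use itself a violation. The same rule names antibiotics among the drugs for which the visit is prolonged, so on that reading it would never apply to them.

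**2. A participant who stops early and is re-treated.** Eighty percent of 14 days is 0.80 × 14 = 11.2 days. Someone who stops before then is a violator under section 2.6, so the prolonged visit in section 2.3 does not plainly apply. The article does not say whether the participant is still tested or, if so, how a negative result counts in ITT and modified ITT.

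**3. The plan's own figure.** Inputs from section 2.6: rate 96.2%, margin 8 points, two-tailed 0.05 (one-sided 0.025), power 80%, dropout 10%.

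n = 2p(1−p)(z₀.₉₇₅ + z₀.₈₀)² / m² = 2 × 0.962 × 0.038 × (1.960 + 0.842)² / 0.08² ≈ 89.7, so 90 per arm. Then 90 / 0.90 = 100, which is the stated figure. The steps below use 90 evaluable per arm.

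**4. Size in one arm.** Expected failures at the planned rate: 90 × 0.038 = 3.4 per arm. Let f be the share of the regimen's failures who take a non-study antibiotic before the UBT, and c the chance that it cures them. The observed rate rises by f × c × (1 − p). Both f and c are assumptions; the documents give neither.

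| Share of failures taking antibiotics (f) | Rise at p = 96.2%, c = 30 to 90% | Rise at p = 85%, c = 30 to 90% |
|---|---|---|
| 5% | 0.06 to 0.17 points | 0.23 to 0.68 points |
| 10% | 0.11 to 0.34 points | 0.45 to 1.35 points |
| 25% | 0.29 to 0.86 points | 1.13 to 3.38 points |
| 50% | 0.57 to 1.71 points | 2.25 to 6.75 points |

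Example: 0.10 × 0.60 × 0.038 = 0.0023, or 0.23 points.

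**5. Effect on the comparison.** With the same f × c in both arms, a true difference shrinks by the factor 1 − f × c. At f × c = 0.10 × 0.60 = 0.06, a difference of 8 points becomes 8 × 0.94 = 7.5. With unequal use the shift can go either way.

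As a one-sided illustration, let the modified arm be truly 8 points worse (88.2% against 96.2%, 90 per arm) and let only that arm gain. The chance of concluding non-inferiority at one-sided 0.025 is Φ((0.08 − d)/SE − 1.96), where d = 0.962 − (0.882 + f × c × 0.118) and SE is the unpooled standard error.

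| f × c | d (points) | Chance of concluding non-inferiority |
|---|---|---|
| 0 | 8.00 | 2.5% |
| 0.05 | 7.41 | 3.5% |
| 0.10 | 6.82 | 4.9% |
| 0.25 | 5.05 | 12.7% |

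If the tetracycline arm gained instead, non-inferiority of the modified regimen would be harder to conclude, not easier.

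**The case against.** **The article is a condensation.** A full list of PP deviations, CRF fields and sensitivity analyses commonly sits in the full protocol or SAP. This is fair, and their absence alone would not be a finding. But the article does state how post-regimen antibiotics are handled and does state what a violation is. Together those two rules produce the misclassification. If the full documents name antibiotics as a violation, the article's definition only needs to be aligned with them.

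**Using the observed status regardless of later treatment is a recognised ITT choice.** This also stands. It is a reason not to count incidental-antibiotic cases as failures in the main ITT analysis. It does not defend the PP set, which is meant to reflect the regimen taken as planned.

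**The effect is small.** Of 3.4 expected failures, if 10% took antibiotics and half of those were cured, that is 3.4 × 0.10 × 0.50 = 0.17 participants, or about 0.2 points. This stands as well. Nothing in the article shows that a single incidental course cures; the regimens it discusses are combinations.

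**Stronger readings that a reader might infer:**

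- *Early stoppers rescued by a second regimen are credited to the arm they abandoned.* The text does not say this. It speaks of antibiotics that may affect the test, not of re-treatment, and the proviso plausibly shuts out those below 80%. They are also outside PP.
- *The tetracycline arm gains more, because the modified regimen is better tolerated.* The Discussion does say that "this therapy has fewer adverse events and higher compliance than does bismuth-containing quadruple therapy". It is reporting an earlier study of rescue treatment after at least 2 failures, not an expectation for this first-line trial.
- *The shift could approach the margin.* Suppose 10% of one arm and 3% of the other stop early, all remain infected, all are re-treated and 80% are cured. That gives 0.10 × 0.8 = 8.0 points against 0.03 × 0.8 = 2.4, a net 5.6. Every input is assumed, and the scenario depends on the early-stopper reading that the proviso puts in doubt.

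**Conclusion.** The point holds in a limited form. As written, a compliant participant who is cured by a non-study antibiotic before the UBT stays in PP and counts as a success of the allocated arm, because a washout corrects suppression and not clearance. Separately, the ITT and modified ITT status of a participant who stops early and is given another eradication regimen before the UBT is unclear.

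The size is unknown and probably small: a few tenths of a point at the planned 96.2%, if the share of failures taking antibiotics is modest. It grows if eradication is nearer 85% or use is heavy. Because the trial is open label, unequal use between arms is possible, but the documents do not show which arm would gain. They support neither a claim that one arm is favoured nor a shift of several points. The change is worth making because it costs almost nothing and removes a known misclassification.

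**What to change.** These changes concern analysis classification and recording only. The UBT timing rule in section 2.3 stays as it is.

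1. In section 2.6, name any non-study systemic antibiotic taken between the first dose and the post-treatment UBT as a second PP violation.
2. State that a participant given another H pylori eradication regimen before that UBT is classified as not eradicated by the allocated regimen in ITT and modified ITT. Say also whether the proviso in section 2.3 is meant to apply to participants below 80% compliance.
3. Record the drug and dates on the CRF, and report such use by arm.
4. Add one ITT sensitivity analysis that counts incidental-antibiotic cases as not eradicated. The main ITT analysis keeps their observed status.

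The cost is a few sentences, one CRF field and one extra analysis, with no added participants or procedures. The downside is a slightly smaller PP set and possibly a slightly lower ITT eradication rate. The rules should be settled before outcomes are analysed.

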### Randomization and blinding

2.4

Eligible patients will be approached during their routine gastroenterology unit visit by the research team for recruitment. A single independent staff member will prepare the randomization sequence, which will be accomplished using a block design and a block size of 4. Randomization of a block will be done by means of a random-number chart. This study is an open-label trial due to the difference in administration method for each arm. The modified quadruple therapy group will have amoxicillin twice a day, whereas the bismuth-containing quadruple therapy group will have tetracycline 4 times a day. Therefore, doctors and participants will be aware of the drugs that are prescribed. However, only the rate of eradication success, adverse events, and compliance with the therapies will be considered outcomes of this trial, and it is believed that an open-label design in itself will not influence the procedure or results of the trial.

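### A fixed block of 4, published during open-label recruitment, lets a recruiter who sees the whole allocation history foresee up to one third of assignments

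*Protocol article*

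**What the plan says.** Section 2.4 (Randomization and blinding) of the protocol article sets out the allocation method. The list is made by one person outside the clinical team: "A single independent staff member will prepare the randomization sequence". It is built "using a block design and a block size of 4", and "Randomization of a block will be done by means of a random-number chart". One size is given, with no variation.

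The same section says the trial is open-label, so that "doctors and participants will be aware of the drugs that are prescribed", and that recruitment is done by the research team: "Eligible patients will be approached during their routine gastroenterology unit visit by the research team for recruitment". It then expresses the belief that the open-label design will not influence the trial, pointing to the outcomes being measured.

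Section 2.1 (Overview of the trial design) adds that "Participants will be recruited from 2 Hallym University-affiliated Hospitals", in two cities, and that "the recruitment period is from August 2018 to July 2019". The article's publication date is 16 November 2018, so the block size became public within that period. Section 2.6 (Statistical analysis) gives the size of the trial: "The calculated number of subjects required for the trial is 100 in each arm".

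The article does not say whether the hospitals share one list or have one each.

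**The concern.** In an unblinded trial, past assignments are known to those who made them. With blocks of one known, small size, the past then reveals part of the future. In a 1:1 block of 4 the last place is always determined, and the third is determined whenever the first two went to the same arm. Independent preparation of the list does not prevent this, because the prediction uses assignments already made and needs no sight of the list.

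A recruiter who can foresee the next arm can, even without intending it, delay or pass over a particular patient. The article contains a belief on which this could act: the Discussion reports that, in an earlier study of rescue treatment, modified quadruple therapy had fewer adverse events and better compliance than bismuth-containing quadruple therapy. Patients thought less tolerant or less adherent could be steered by anticipated arm. All three outcomes named in section 2.4 (eradication, adverse events, compliance) are open to that.

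A few patients matter here. The planning assumptions leave 90 evaluable patients per arm, with 90 × 0.038 = 3.4 expected failures. The 8-point margin corresponds to 0.08 × 90 = 7.2 patients. This shows how sensitive the comparison is; it does not estimate a bias.

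**Working it through.** **Inputs.** Block size 4 (section 2.4); 100 per arm, so 200 in total and 1:1 allocation (section 2.6); two hospitals (section 2.1); 96.2% eradication, 8% margin, two-tailed α 0.05, power 80%, 10% dropout (section 2.6).

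**The plan's own figure.** The article gives no figure for predictability. Its one design figure, 100 per arm, can be reproduced by taking 96.2% in both arms (an assumption):

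n = 2 × 0.962 × 0.038 × (1.960 + 0.842)² / 0.08² ≈ 89.7, so 90 per arm; 90 / 0.9 = 100.

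The sample size is not in dispute. It serves only to fix the total of 200, or 200 / 4 = 50 blocks.

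**Certain allocations when all earlier assignments are seen.** A block of 4 with two of each arm has 6 equally likely orders.

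- Places 1 and 2: never certain.
- Place 3: certain if the first two match, which happens in 2 of 6 orders, probability 1/3.
- Place 4: always certain.

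Expected certain places per block: 1/3 + 1 = 4/3. As a share: (4/3) / 4 = 8/24 = 33.3%. Over 50 blocks: 50 × 4/3 ≈ 67 of 200.

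**Best-guess rate, same observer.** The observer always names the arm that is behind in the block, and tosses a coin when the arms are level.

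- Place 1: 1/2.
- Place 2: 2/3.
- Place 3: (1/3 × 1) + (2/3 × 1/2) = 2/3.
- Place 4: 1.

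Mean: (0.500 + 0.667 + 0.667 + 1) / 4 = 70.8%, against 50% by chance.

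**One list shared by two hospitals, with no exchange of allocations.** Assume a recruiter sees each earlier allocation with probability f (the hospital's share of recruitment) and knows the position on the list. Certainty requires having seen both members of the matching pair, so each probability above is multiplied by f²:

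certain share = f² × (1/3 + 1) / 4 = f²/3.

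- f = 0.50: 8.3% (about 17 of 200 over both hospitals).
- f = 0.75: 18.8% at the larger hospital; f = 0.25: 2.1% at the smaller.
- f = 0.90: 27%.
- f = 1: 33.3%. This is also the case of a separate list per hospital.

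If recruiters do not know list positions, the share is lower than these values.

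**Effect of varying the block size.** This was simulated with 1,500 lists of 200, sizes drawn with equal probability, and an observer who knows the set of sizes and sees the full history.

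- Fixed 4: 33.3% certain, 70.8% best guess.
- Sizes 4 and 6: about 5.4% certain, about 69%.
- Sizes 4, 6 and 8: about 2.2% certain (0.022 × 200 ≈ 4 patients), about 68%.

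Lists of 100 give almost the same results. For comparison, exact enumeration of a single fixed size of 8 still gives 20% certain and 66.6% best guess. Variation, more than size, is what removes certainty.

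**The case against.** The strongest objection is to the one-third figure itself. It needs a recruiter who sees every earlier allocation on the list. The article says doctors know what is prescribed; it does not say that doctors at one hospital learn what is prescribed at the other. Section 2.4 speaks of the sequence in the singular, which may mean one common list, and then the certain share is about 8% at equal recruitment. This stands: a reader might infer that a third of allocations are certain as a matter of fact, but the document supports that only as an upper limit.

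A reader might also infer that bias has occurred. Nothing shows that. Section 2.2 lists explicit exclusions, including earlier allergy or adverse reaction to the study medicines, which narrows the room for steering on tolerability. Section 2.3 reads eradication from a breath test with a numeric cut-off, which limits biased assessment. Neither prevents selective enrolment of eligible patients, so the risk remains.

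Finally, a reader might infer that allocation is not concealed, or that the analysis wrongly ignores hospital. The article does not support either reading. How each assignment is released, whether lists are per hospital, and any adjustment for hospital are details that a condensed article commonly leaves to the full protocol or the SAP. The point rests on what is stated: one fixed size, made public, in an unblinded trial.

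**Conclusion.** The point holds as a design weakness that is cheap to reduce. A single block size of 4, stated publicly during open-label recruitment, lets a recruiter with the full history of a list foresee up to 33.3% of assignments (about 67 of 200) and guess the next arm with 70.8% success. The upper limit applies if each hospital has its own list or if allocations are shared between hospitals. With a common list, equal recruitment, no sharing and known list positions, the certain share is 8.3%, and less if positions are unknown.

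The figures assume 1:1 blocks and a recruiter who knows the block size. The second assumption is plausible: the article that gives the size also describes, in the first person, the recruitment its authors are conducting. What follows is a risk of selective enrolment. Its effect on the eradication difference cannot be estimated from the document.

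**What to change.** For participants still to be randomised, the existing independent staff member should replace the fixed block of 4 with randomly varying block sizes, for example 4, 6 and 8, and the sizes should not be disclosed to recruiters. If the hospitals have separate lists, this is needed all the more, because each recruiter's view of the local list is then complete.

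The gain is uneven. Certain allocations fall from up to 33.3% to about 2%, even if the set of sizes becomes known. The best-guess rate falls only from 70.8% to about 68%, so the change removes most of the certainty and little of the guessing advantage.

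Costs: a new list, with no extra staff. An incomplete last block of 8 can leave the arms at most 4 patients apart on a list, against 2 with blocks of 4. Because the ministry and both hospitals' review boards approved the protocol before the start (section 2.8), the change also needs an amendment, which should not itself reveal the sizes to recruiters.
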